### Control group

3.4

All participants in the control group will complete all evaluation measures at each time point. Control participants will also be required to complete informed consent prior to collecting any measurements.

### Evaluation

3.5

All evaluation measurements will be taken at baseline, approximately 7 weeks and then again approximately 14 weeks after commencement of intervention (we say approximately as the timing depends on when the patients scheduled appoints occur).

### Measures

3.6

After randomisation a trained research assistant will collect baseline data on participants demographic data including age, sex, education, current employment status, marital status and living arrangement (who they live with), and ethnicity by way of survey. Participants’ waist circumference (WC), height and weight (to calculate body mass index) will also be recorded. As well as body fat percentage and muscle mass using bio-impedance scales. Handgrip strength will be recorded using the handheld dynamometer. Fatigue will be assessed using the 13-item fatigue subscale of the Functional Assessment of Chronic Illness Therapy-Fatigue (FACIT-F) questionnaire [20]. Sleep will be assessed using the Pittsburgh Sleep Quality Index [21], an 18-item questionnaire which assesses sleep quality and disturbances over a 1-month time interval. Quality of life will be assessed using the five-level EuroQol-5D questionnaire (EQ-5D-5L) [22]. Finally, participants will be fitted with the Actigraph accelerometer to measure free-living physical activity over 7 consecutive days. Follow-up data will be collected at 7 weeks and 14 weeks.

Patients randomised to the control comparator will receive ‘usual care’ and undergo all baseline and follow-up measures.

Levels of free-living physical activity will be assessed using the Actigraph accelerometer (GT3X) at each data collection point. The Actigraph accelerometer is a valid and reliable tool to monitor free-living physical activity and its validity and reliability has been shown in multiple populations [23]. The Actigraph GT3X is worn on a belt around the waist with the device itself positioned above the right hip either over or under clothing. We will employ a sampling frequency of 30 Hz. Service users will be asked to wear the device during waking hours every day for seven consecutive days, but not during water-based activities or sleep.

In addition to the above we will also collect data on the following variables: number of patients screened, proportion of patients enrolling, and number of patients who dropout of the study.

Those in the intervention arm will also be asked to take part in one semi-structured qualitative interview. Interviews will explore experiences of the intervention including barriers and facilitators to compliance, satisfaction and perceived effectiveness of the different elements of the intervention, and suggestions for improvement. All interviews will be audio recorded and transcribed. With the consent of participants, semi-structured interviews will be conducted. We anticipate that each interview will take approximately 30–45 min. Interviews will be digitally recorded, and transcripts will be anonymized for identifiable information.

### Analysis

3.7

#### Outcome

3.7.1

The primary outcome for this study will be indicative change in average daily time spent in sedentary time, light physical activity and moderate-to-vigorous physical activity (MVPA) as recorded by the Actigraph accelerometer. Other secondary outcomes collected using participant questionnaires and objective measures include: (1) indicative change in WC and BMI, (2) indicative change in fatigue, sleep and QOL, (3) indicative change in grip strength.

### Sample size

3.8

The aim of the present study is to pilot the proposed intervention and if promise is observed we plan to secure further funding to incorporate the intervention booklet into a mobile application that we will subsequently run a fully powered RCT. As in this scenario we are predominantly interested in “promise” we will recruit and trial the intervention in a sample of 30 participants (15 in the control arm and 15 in the intervention arm). It should be noted here that findings from this pilot will be used to inform the power calculation for the full trial.

### Data analysis-Quantitative

3.9

We will summarize all data by treatment group. Statistical measures of central tendency and dispersion such as mean, standard deviation (continuous variables), frequency distribution, interquartile range (IQR) and median (categorical variables) will be used in descriptive statistics. Non-parametric statistical methods will be used for bivariate analysis. Stata version 16 software will be used to perform the analysis.

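### Section 3.9 plans only unadjusted non-parametric bivariate analysis of change, with no baseline-adjusted arm difference and confidence interval to serve the pilot's stated purpose

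*Protocol article*

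**What the plan says.** Section 3.9 of the protocol article has two analytic elements. The first is descriptive: "We will summarize all data by treatment group", with means and standard deviations for continuous variables. The second is comparative: "Non-parametric statistical methods will be used for bivariate analysis". No test, covariate, model or interval estimate is named.

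On outcomes, section 3.7.1 says: "The primary outcome for this study will be indicative change in average daily time spent in sedentary time, light physical activity and moderate-to-vigorous physical activity". The secondary outcomes there (waist circumference and BMI; fatigue, sleep and quality of life; grip strength) are also framed as change. On timing, section 3.5 says: "All evaluation measurements will be taken at baseline, approximately 7 weeks and then again approximately 14 weeks after commencement of intervention".

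On purpose, section 3.8 sets 30 participants, 15 per arm, in order to look for promise, and adds that "findings from this pilot will be used to inform the power calculation for the full trial". Section 3 describes simple random allocation and mentions no stratification.

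**The concern.** Judging promise and planning a larger trial both call for an estimated arm difference, its uncertainty, and the variance on the scale the full trial will use. Bivariate analysis takes two variables at a time, so it has no place for baseline as a covariate. Applied to change scores, it uses baseline only by subtraction, which fixes the baseline slope at 1. When the true slope is below 1, subtraction removes too much of any chance baseline difference, and the excess stays in the result as noise. Such differences can be large with 15 per arm and unstratified allocation.

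At stake are some of the precision in an already small study and the direct reporting of what the full-trial calculation needs. A p-value is a poor substitute for an interval at this size.

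**Working it through.** **Inputs from the document.** 15 per arm (section 3.8); simple allocation (section 3); outcomes as change (section 3.7.1), taken here to mean change from baseline; measurements at baseline and about 7 and 14 weeks (section 3.5). The sample of 30 comes with no alpha, power, effect size or SD, so there is no stated figure to reproduce.

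**Assumptions, not in the document.** Baseline-follow-up correlation r of 0.5 to 0.7, with 0.3 and 0.8 as outer values; equal variances at baseline and follow-up; no dropout; two-sided alpha of 0.05.

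**1. Chance imbalance.** The standard error of the baseline difference is sqrt(2/15) = 0.365 SD. The 95% range is ±1.96 × 0.365 = ±0.72 SD.

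**2. Over-correction by change scores.** With equal variances the expected slope of follow-up on baseline is r, but subtraction uses 1. A baseline difference D therefore shifts the change comparison by (1 − r) × D in the opposite direction. For D = 0.72 SD the shift is 0.36 SD at r = 0.5 and 0.22 SD at r = 0.7. Averaged over randomisations this is not bias. It is extra variance.

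**3. Variance.** In units of the outcome variance, a change score has 2(1 − r) and ANCOVA has 1 − r². The ratio is (1 + r)/2, and the equivalent gain in participants is 1/ratio − 1. The 95% half-widths use t with 28 df (change) or 27 df (ANCOVA), multiplied by sqrt(2/15 × variance).

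| r | Change variance | ANCOVA variance | Ratio | Equivalent gain | Half-width, change (SD) | Half-width, ANCOVA (SD) |
|---|---|---|---|---|---|---|
| 0.3 | 1.40 | 0.91 | 0.65 | 54% | 0.89 | 0.72 |
| 0.5 | 1.00 | 0.75 | 0.75 | 33% | 0.75 | 0.65 |
| 0.7 | 0.60 | 0.51 | 0.85 | 18% | 0.58 | 0.54 |
| 0.8 | 0.40 | 0.36 | 0.90 | 11% | 0.47 | 0.45 |

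Check: the two variances differ by 2(1 − r) − (1 − r²) = (1 − r)², the contribution of step 2. The imbalance and the lost precision are one effect, not two.

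**4. Small-sample cost.** The ratios in step 3 treat the slope as known. With 30 patients and a normally distributed baseline, estimating it inflates the ANCOVA variance on average by 1 + 1/(30 − 4) = 1.038. The ratios become 0.75 × 1.038 = 0.78 and 0.85 × 1.038 = 0.88, or gains of about 28% and 13%. The direction is unchanged.

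**5. What a test can tell.** For a two-sample comparison with 15 per arm (normal approximation), power is 28% for a difference of 0.5 SD and 59% for 0.8 SD. Reaching 80% power needs about 1.02 SD. A non-significant result would say little about promise.

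**The case against.** The case on the other side is substantial, and several parts of it stand.

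- **Baseline is not ignored.** A reader might infer that it is. Outcomes defined as change use it, so the proper comparator for ANCOVA is the change score. The larger gain over a follow-up-only comparison (1/(1 − r²) − 1, or 33% to 96% at r = 0.5 to 0.7) answers an analysis the document does not describe.
- **A variance will be available.** A reader might infer that none is. The planned summaries give SDs by arm and a crude mean difference. If the SD of change is reported with the visit SDs (s₁ at baseline, s₂ at follow-up) for the same patients, r follows as (s₁² + s₂² − s_change²)/(2·s₁·s₂), and the residual SD as s₂·sqrt(1 − r²). Section 3.9 does not commit to reporting them that way, so direct reporting is still worth asking for.
- **The arm comparison is inferred.** Section 3.9 does not name what is compared with what. Between arms is the natural reading in a two-arm trial summarised by group, but it remains a reading.
- **This is a condensed article.** A fuller document may name tests, intervals and models. However, restricting the comparison to bivariate analysis is a stated choice. An adjusted primary model would depart from it, not fill in a detail.
- **Rank methods are defensible.** They can yield an interval, such as a Hodges-Lehmann shift, though the article states none and it would not be baseline-adjusted. The Introduction cites median MVPA of 0.0 to 5.2 min/day in prostate cancer survivors. If MVPA here is similarly near zero, a linear model with one residual SD is questionable and the gains above may not apply. This is why resampling-based inference and a retained rank test belong in the remedy.
- **No decision rests on a p-value.** The article states no hypothesis or threshold, which limits the harm.

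**Conclusion.** The point holds as a worthwhile improvement at low cost. It is not an error that would invalidate the pilot. The one stated comparison is non-parametric and bivariate, hence unadjusted, and no baseline-adjusted arm difference with a confidence interval is planned, although the study is meant to judge promise and feed a power calculation.

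Against a change-score analysis, baseline adjustment would cut the variance to 0.75 to 0.85 of its value, equivalent to about 33% to 18% more participants (about 28% to 13% after the small-sample cost). These figures rest on an assumed correlation of 0.5 to 0.7, equal variances, no dropout and a roughly linear relation. They are least secure for MVPA. The document does not support the stronger claims that baseline data are discarded or that the full trial would have no variance estimate.

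**What to change.** Reword section 3.9 to state the following.

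- For each outcome, the arm difference is estimated from a model of the follow-up value on arm and baseline value, or from one repeated-measures model of weeks 7 and 14 with baseline included. Participants are analysed by arm as randomised.
- The adjusted difference is reported with a 95% confidence interval, using bootstrap or permutation methods for skewed MVPA.
- The residual SD and the baseline-follow-up correlation are reported alongside the planned group SDs, for use in the full trial's power calculation.
- The rank test is kept as a sensitivity check.

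No new data, visits or participants are needed, because baseline and both follow-ups are already collected. The cost is one or two degrees of freedom and a little more analysis work, which the Stata software named in the article can handle.

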### Data analysis-qualitative

3.10

Content analysis will be the first analysis method used but where possible other thematic analysis such as Framework analysis or Interpretative Phenomenological Analysis may also be conducted to fit study objectives. QSR Nvivo software will be used for data management.

### Patient and public involvement

3.11

The exercise intervention was developed through an iterative process and consultation with input from patients, health professionals (urologists, oncology physiotherapist, personal trainers) and experts (academics) in the field. Moreover, this study will interview patients on study exit to further precise the intervention.

### Ethical considerations and dissemination

3.12

Explicit written informed consent will be sought from all study participants. All participants will be informed that they have the right to withdraw from the programme at any point without giving reason.

The results of this evaluation will be disseminated to academic audiences through presentations at national and international conferences in physical activity, public health and medicine and through peer-reviewed publications in relevant journals. Results will be disseminated to the public, policy makers, and other charities through seminars and press releases co-ordinated through the Anglia Ruskin University Press Office.

Ethical approval was obtained for the present study via The London- City and East Research Ethics Committee (ID:291676).

## Discussion

4

The present protocol is to pilot a home-based exercise intervention co-created through an iterative process and tailored specifically for bladder cancer survivors to improve physical and mental health outcomes in this population. If the intervention shows promise we will subsequently incorporate the intervention booklet into a mobile application and run a fully powered RCT.

A clear strength of this study will be the utilisation of a home-based exercise intervention tailored specifically for bladder cancer survivors to promote physical activity and implementing the intervention from the point of diagnosis (approximately one week after). However, some limitations may exist. First, owing to the “high-risk” population we may experience a high level of drop out or a low uptake. It is possible that as someone goes through bladder cancer treatment taking up physical activity may not be a priority for them. Second, the Actigraph GT3X are calibrated to record ambulatory activity (hip movement) and therefore underestimate the intensity of some activities. Third, bladder cancer is most common among older adults who also have a high prevalence of multiple non-communicable diseases which may further impact their ability to engage in a home-based exercise program.[24].
